### 3 INTRODUCTION

#### 3.1 Disease and current treatment

Herpes Simplex Virus (HSV) type 2 is the major infectious agent that causes genital herpes (GH). Epidemiological studies estimate the incidence of acute GH infection in Europe and the United States to be between 5 and 24 cases per 100 people per year ([Malkin, 2004](#)). GH is characterised by the formation of blistering lesions associated with significant pain and discomfort. After an acute episode, the virus may persist in the body as a latent infection in dorsal root ganglia (Johnston 2011). The virus may reactivate, causing migration of virus to the mucosal surface and an outbreak of GH associated with lesion formation, pain and itching. Viral shedding may result in transmission of infection to a sexual partner (Mertz 2008). GH may also be passed from an infected mother to her new-born child in utero, peri-partum and post-partum. Most transmission occurs at the time of birth (Kimberlin 2007). In severe cases HSV infection can result in encephalitis, meningitis and even death. Genital herpes has recently been found to be strongly linked with HIV transmission in Africa ([Abu-Raddad et al., 2008](#)).

To date, treatments have failed to eradicate HSV in an infected individual. Antiviral medications have been shown to reduce the frequency, duration, and severity of outbreaks. Available drugs include acyclovir, valaciclovir, famciclovir, penciclovir, and docosanol. However, these treatments have been unable to eliminate outbreaks or completely prevent shedding. Recurrence of active lesions and asymptomatic viral shedding may therefore result in continued transmission of disease.

DNA vaccines consist of bacterial plasmids, small double strands of non-chromosomal DNA, inserted with gene sequences that encode for specific surface proteins of the target infectious agent. The plasmids typically also contain a unique promoter sequence. Injection of the plasmid into the nucleus of host cells results in transcription and translation of the gene into copies of viral proteins. The foreign antigen complexes are subsequently presented at the host cell surface allowing the immune system to detect and recognize them. A range of immune responses result, including migration of the foreign antigen: immune cell complex to the lymph node.

Previous clinical trials of HSV DNA vaccines have failed to produce a significant or complete reduction of outbreaks or viral shedding, despite induction of high antibody titres (Corey et.al 1999). It is believed that an antibody response needs to also be accompanied by a strong cell mediated immune response.

It is increasingly believed that the ability to potentiate a HSV-2 specific cell mediated immune response will be a critical component of any successful therapeutic HSV-2 vaccine. Such a treatment would result in reduced recurrence, transmission and potential life- threatening herpes infections.

#### 3.2 COR-1

This is a brief summary of the preclinical and clinical profile of COR-1. More detailed information is available in the Investigator's Brochure.

Admedus' HSV vaccine (COR-1) is a 1:1 mixture of two DNA plasmids formulated in sterile, isotonic and endotoxin-free TE buffer. Both plasmids comprise the Nature Technology Corporation (NTC) expression vector NTC8485 minus the enhanced green fluorescent protein sequence. The first has a codon optimised DNA sequence insert encoding full length glycoprotein D from HSV-2 (gD2) (named NTC8485-O2-gD2) and the other with a codon optimised DNA sequence insert encoding one ubiquitin repeat fused to the N-terminal end of amino acids 25-331 of truncated gD2 (named NTC8485-O2-Ubi- gD2tr).

COR-1 differs from other vaccines in development for the treatment of HSV-2 as it is designed specifically to generate both humoral (antibody) and cellular (T-cell) immune responses to the primary surface glycoprotein antigen gD2 of HSV-2. This immune response is expected to better control and protect against HSV-2 infection than either humoral or cellular response alone.

There have been previous concerns regarding the use of DNA vaccines including the possibility of integration into the host genome potentially resulting in tumors. There is however no evidence of integration of plasmid DNA into the host genome making the development of tumor's unlikely (Manam et al., 2000).

Concerns also have arisen regarding the potential to transfer of antibiotic resistance. COR-1 utilizes an antibiotic-resistance free plasmid.

COR-1 has been manufactured by VGXI Inc. (The Woodlands, Texas USA) according to current Good Manufacturing Practice (GMP) standards and is supplied in 2mL, 13mm Type I, Clear, Borosilicate w/ blowback vials (Schott #68001022) with Stopper 13mm Westar RS, S2-F451, 4432/50 w/ Flurotec & B2-40, Grey (West # 19700004) and Seal: 13mm Flip-Off® TruEdge® Long (West #54131335, Royal Blue). The solution in the vial is clear and colourless. Please refer to the IB and Certificate of Analysis (COA).

COR-1 is to be stored at -20 degrees Celsius [°C] +/- 5°C,

### **3.2.1 Pharmacology**

#### **3.2.1.1 *In vitro* Pharmacology**

There is no *in-vitro* experimental data supporting the use of COR-1. In humans, DNA containing unmethylated CpG (such as bacterially-produced plasmid DNA) can selectively enhance Th1 cytokine responses as the CpG repeats may be recognized as pathogen-associated molecular patterns (PAMPs) by toll-like receptor 9 on B cells and certain dendritic cells. While the plasmids in COR-1 were not specifically engineered to contain CpG motifs, unmethylated CpG repeats are present. Unmethylated CpG has been shown to greatly improve the immunogenicity of DNA vaccines, acting as an internal adjuvant. Given that a number of DNA vaccines, including COR-1, containing bacterially-produced plasmid DNA have been tested in humans at much higher dose levels than utilised in our previous Phase I trial and that a number of these vaccines incorporated the pVAX1 plasmid (refer to [www.clinicaltrials.gov](http://www.clinicaltrials.gov)), which is known to contain unmethylated CpG motifs, it is unlikely that COR-1 will induce a toxic Th1 cytokine profile in HSV-2 positive patients. In addition, oligodeoxynucleotides containing unmethylated CpG motifs designed to be used as adjuvants have been shown to be safe in humans (for reviews see Klinman et al., 2010 or Bode et al., 2011).

#### **3.2.1.2 *In vivo* Pharmacology**

In a mouse challenge model of HSV-2 infection, COR-1 has been found to be 100% protective, and 4 out of 9 mice vaccinated had no detectable HSV-2 viral genomes in the dorsal root ganglion at 50x lethal dose (LD)50. In a second study, a vaccine with the same inserted gene sequences but a different expression vector proved to be 100% protective and able to confer sterilising immunity in 4 of 10 mice at a challenge dose of 50x LD50. Please refer to the IB for further information.

### **3.2.2 Preclinical Safety**

#### **3.2.2.1 *In vitro* Safety**

There have been concerns regarding the use of DNA vaccines including the theoretical possibility of integration into the host genome potentially resulting in tumours. However, no evidence of integration of plasmid DNA into the host genome has been observed in any DNA vaccine trial, making the development of tumour's unlikely (Manam et al., 2000).

Additionally there have been concerns with DNA vaccines that contain antibiotic selection markers having the potential to facilitate the transfer of antibiotic resistance from the plasmid to the host

genome or microbiome. To alleviate this concern, the NTC8485 plasmid used for COR-1 does not use an antibiotic-resistance selection marker.

### 3.2.2.2 *In vivo* Safety

A single species, Good Laboratory Practice (GLP) repeated dose toxicity study was conducted in Swiss CD1 mice. Four ID injections of the COR-1 vaccine at 30 or 250 mcg/dose were administered over a 6 week period. Dose-related antibody and inflammatory responses were associated with the administration of the 250 mcg/dose. The inflammatory symptoms had reversed after a 3-week treatment free period. There was no evidence of any systemic organ toxicity.

The no observed adverse effect level (NOAEL) based on absence of relevant adverse effects at the highest dose studied in toxicology experiments in mice was 250 mcg/mouse (repeat dose toxicology studies). This equates to a NOAEL of 12.5 mg/kg in the mouse (assuming a 20 g mouse weight). To get the human equivalent dose (HED), the NOAEL is divided by 12.3 (FDA Guidance for Industry: Estimating the Maximum Safe Starting Dose in Initial Clinical Trials for Therapeutics in Adult Healthy Volunteers), which equals a human dose of 1.016 mg/kg or a total dose of around 70mg for a 70kg human. As such, for this study, there is an approximate 140 fold safety margin compared with the 500 mcg dose and approximately 70 fold for the proposed maximum human dose of 1 mg.

### 3.2.3 Metabolism and pharmacokinetics

#### 3.2.4 Clinical trials of COR-1

The primary objective of the previous Phase I, single ascending dose study was to examine the safety and tolerability of a 3 dose regimen of COR-1 administered intradermally (ID) to healthy, non-HSV-2 infected sero-negative volunteers. In addition the study investigated whether COR-1 induced anti-HSV gD2 specific antibodies and/or produced a cell-mediated immune response to gD2 in this population. This dose escalation study aimed to identify an optimal dose of COR-1 required for induction of an efficacious immune response which could protect against future HSV infection.

A total of 22 subjects were enrolled in the study and received at least one dose of COR-1 vaccine. All subjects were included in the Safety Analysis. Twenty subjects received 3 doses of vaccine and were included in the Per Protocol Analysis. A total of 35 Treatment Related Adverse Events (TEAEs) were reported during the study period by 15 subjects (68.2%). A greater number of TEAEs were reported for the 1 mg COR-1 group (19 events) compared with the 10 mcg, 30 mcg, 100mcg and 300mcg COR-1 groups (between 2 and 7 events).

One SAE was reported in the 1 mg COR-1 group (clavicle fracture). This event was considered not related to the COR-1 vaccine and no action was taken with the study drug.

The most frequently reported TEAEs were classified under the following System Organ Classes (SOCs):

- Skin and subcutaneous tissue disorders (10 events reported by 3 subjects in the 1 mg COR-1 group only). Skin hyperpigmentation (at the injection site) was the only TEAE reported in this SOC.
- Nervous system disorders (7 events reported by 6 subjects). Events in this SOC were observed in all treatment groups except the 30 mcg COR-1 group

The majority of TEAEs experienced were classified as mild (30 events). Three events reported in the 1 mg COR-1 group were classified as severe. These events were related to the SAE of clavicle fracture. There were no trends identified by treatment group or severity for the TEAEs reported. The majority of TEAEs were considered not related or unlikely to be related to the COR-1 vaccine. 10 events of skin hyperpigmentation observed in the 1 mg COR-1 group were considered definitely related to the COR-1 vaccine.

A total of 143 local ADRs were reported during the study period by 21 subjects (95.5%). The number of local ADRs reported increased with increasing dose of COR-1. Erythema and induration were the most frequently reported injection site reactions, occurring in at least one subject in each treatment group at some point during the vaccination phase. Erythema was reported more frequently in the 100 mcg, 300 mcg and 1 mg COR-1 treatment groups. Induration was reported more frequently in the 1 mg COR-1 treatment group. All injection site reactions were classified as mild in intensity.

A total of 14 systemic ADRs were reported during the study period by four subjects (18.2%). The most frequently reported were headache, fatigue, chills, malaise, pain and pyrexia. There were no trends in the frequency of systemic ADRs by treatment group. All the systemic ADRs reported were classified as mild in severity.

Review of haematology and biochemistry results revealed no trends or notable changes over time following vaccination with COR-1 at any dose level. There were no trends or notable findings in vital signs following each vaccination with COR-1 at any dose level.

A review of the safety data suggests that 3 ID vaccinations of the COR-1 vaccine at three weekly intervals were safe and well tolerated.

No anti-HSV gD2 antibodies were detected in any subject by ELISA, indicating that no subjects had seroconverted to COR-1 during the study based on the utilised method.

IFN- $\gamma$  production by T cells specific for gD2 antigen was induced in 19 of the 20 subjects who completed the study as planned and was considered a cell-mediated response to the COR-1 vaccine. The response rates were similar in all treatment groups with 100.0% of subjects responding to the COR-1 vaccine in the 10 mcg, 30 mcg, 300 mcg and 1 mg groups and 75.0% responding in the 100 mcg group.

A post hoc analysis was performed on the size of the erythema observed from the photographs taken of the injection sites at one and two days after each vaccination. The analysis revealed that at the higher doses of the vaccine, the size of the erythema increased on day 2 compared to the size of the erythema observed at day 1. This phenomenon was also observed in some subjects receiving the lower doses, but not in the 10 mcg dose. This would indicate a Delayed Type Hypersensitivity reaction, which is a cell mediated immune response and not an antibody-mediated response. This is not inconsistent with the lack of antibody response observed and supports the cell mediated immune response observed.

The analysis of the photographs also revealed a dose response with the size of the erythema observed increasing with increasing doses of the COR-1 vaccine.

Given that no anti-HSV gD2 antibodies were detected in any subject, an optimised dose of COR-1 in order to promote an antibody response to protect against future HSV infection cannot be ascertained. However, COR-1 vaccine did induce a cell-mediated immune response at all doses and this information, together with the safety data and the post hoc analysis of size of the erythema at the injection site, can be used to predict an optimised dose of COR-1 to potentially treat an existing HSV infection.

### 3.3 Rationale for the Study and Dose Selection

COR-1 in the previous Phase I study was well tolerated in healthy volunteers administered three vaccine doses up to 1mg/administration at three weekly intervals. The proposed dose levels/administration to be utilised in this study will not exceed this 1 mg dose.

The dosing interval to be utilised has been increased from three to 4 weekly. The rationale behind this interval change is the anticipation that the subjects may find this schedule easier to maintain. Subjects in this study will receive an additional dose of vaccine half way through the study (Week 24) to both confirm its safety and tolerability and to probe the longevity of the generated immune response and the need for such a booster vaccination. Subjects will be monitored for immunological and clinical signs of vaccine efficacy pre- and post- the booster vaccinations to further understand the effect of this investigational vaccine in subjects with recurrent HSV-2 infection.

## 4 OBJECTIVES AND ENDPOINTS

### 4.1 Objectives

The primary objectives of this study are to:

- Evaluate the safety and tolerability of two injection regimens of the HSV-2 DNA vaccine COR-1 compared with placebo, administered by intradermal injection as three, 4-weekly doses followed by a 6-month booster to otherwise healthy symptomatic HSV-2 positive subjects.

The secondary objectives are:

- To investigate the impact of COR-1 on:
  - Induction of an antigen specific humoral and/or cell mediated immune response against gD2.

The exploratory objectives of this study are to evaluate:

- The effect of COR-1 on HSV-2 shedding;
- The incidence of symptomatic HSV-2 genital recurrence; and
- The nature of the immunological responses to COR-1, including local tissue responses.

### 4.2 Endpoints

#### Primary endpoints:

The primary endpoints of this study are:

- Incidence and severity of adverse events in each treatment group, including vaccine related adverse events:
  - Incidence and severity of local reactions (soreness, redness, induration, ecchymosis, oedema, itching and paraesthesia) at the site of vaccination;
  - Incidence and severity of systemic reactions (fatigue, myalgia, malaise, fever, rigors, arthralgia, nausea, diarrhoea, light headedness, dizziness, hypersensitivity and headache).

#### Secondary endpoints:

Immunogenicity:

- Change from Baseline in T-cell and/or antibody responses to HSV-2 gD2 as measured by:
  - ELISA (antibody);
  - Interferon-gamma (IFN $\gamma$ ) enzyme linked immunospot (ELISPOT) assays (T-cell responses).

#### Exploratory endpoints:

Efficacy:

- Number of days with detectable viral shedding after 3-dose vaccination, compared with Baseline.
- Number of days with detectable viral shedding after the booster injection compared with Baseline.
- Symptomatic genital herpes recurrence rate:
- Time to first recurrence of symptomatic genital herpes measured from first administration of study vaccine;
- Number of symptomatic recurrences of genital herpes during the course of the study (to Week 48).
- Viral load level after three dose levels compared to baseline
- Viral load level after booster compared to baseline

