## 4.3 Study Design

This is a randomized single or multi centre, double blind, placebo-controlled, parallel group pilot study to assess the safety and efficacy of a therapeutic HSV-2 DNA vaccine in HSV-2 positive adults. Subjects will be randomized to receive either COR-1 or placebo using a 3:1 allocation ratio. Treatment assignment to either COR-1 or placebo will be double-blinded. There will be 2 Groups of subjects. Group 1 will receive one injection into each forearm. Once this group has been fully allocated, Group 2 will commence recruitment. Group 2 will receive two injections to the one forearm.

There are two primary reasons for inclusion of the 2 placebo arms:

- To maintain the blind; and
- To describe any natural variation in viral shedding rates between the baseline shedding assessment pre- and post-administration of the placebo.

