### 5.2 Inclusion Criteria

The criteria for entry into the study are:

1. Diagnosis of genital HSV-2 infection confirmed by positive HSV-2 serology or if negative a documented positive HSV-2 pathology result, AND positive PCR for HSV-2 during the Baseline Shedding Assessment prior to randomisation
2. A history of recurrent genital HSV-2 for at least 12 months AND a self-reported history of at least 3 and no more than 9 reported lesion occurrences in the 12 months prior to Screening or, if currently on suppressive therapy, in the 12 months prior to initiation of suppressive therapy.
3. Aged 18 to 50 years, inclusive.
4. Male or female. Women of child-bearing potential must be using two effective methods of contraception and agree to continue to do so from Screening, throughout Investigational vaccine/placebo dosing and for 28 days after the last dose of investigational vaccine/placebo.
5. Has voluntarily given written informed consent.

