#### **6.4.9 Genital viral shedding assessments**

Subjects will be educated regarding genital swab collection, diary booklet completion and HSV-2 outbreak management. The requirement for compliance in these aspects of the study should be reinforced as often as possible. Additional unscheduled visits may be scheduled for educational purposes should the Investigator or designee judge that this is required.

Daily genital swabs to detect viral shedding will be performed for 45 days commencing as follows:

1. Run-in Shedding Assessment - prior to the first vaccination.
2. Post Vaccination Shedding Assessment - commencing one week following the third investigational vaccine/placebo (Study Period 1); and
3. Post Booster Shedding Assessment - commencing one week after the booster vaccination/placebo (Study Period 2).

Prior to commencing the first assessment period, each subject will be given written gender specific instructions for obtaining genital swabs.

The subject will be instructed to take the swabs at the approximately the same time of the day. Ideally this will be before bathing.

If the subject does not collect a swab at the planned time they will be instructed to obtain a swab as soon as they are able to. (Provided it is on the same day). If this is not until the following day, they will be instructed to document in the diary booklet that a swab wasn't collected, and the reason for not doing so.

Subjects will be given sufficient swabs and courier supplies to enable them to collect the required number of daily swabs. Each subject will receive:

- Swabs,
- Tubes containing the transport medium,
- Spare swabs in case of error,
- Sample biological bags,
- Prepaid/pre-labelled return mail packs,
- Requisition forms;
- Sample labels;
- Torch (for inspection of the genital region);
- Mirror (for inspection of the genital region);
- 'HSV-2 Outbreak' kits for when a subject develops lesions. This kit includes:
  - Swabs;
  - Tubes containing the transport medium,
  - Sample biological bags,
  - Prepaid/pre-labelled return mail packs
  - Requisition Forms; and
  - Sample labels.

Gender specific instructions for obtaining genital swabs will be provided to subjects at Visit 2.

In summary, men will be instructed to obtain the following swabs:

1. Penile skin
2. Perianal and rectal areas.

Women will obtain the following swabs:

1. Vaginal and vulval area;
2. Perianal and rectal areas.

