### **6.8.3 Dosage and administration of test drugs**

Subjects are to receive either one or two intradermal injections at four week intervals for 3 vaccinations and a Booster vaccination at approximately 6 months from Baseline (see Section 6.3). Vaccinations will occur at: Baseline, Week 4, 8 and a booster will be administered at Week 24. Subjects in Group 1 will receive the intradermal injections into each forearm. Subjects in Group 2 will receive the intradermal injections to the one forearm.

Further details on the administration of study vaccine will be provided in the Study Reference Manual.

Prior to each injection, the forearm(s) that are to be injected will be examined and findings from this examination will be documented. The proposed injection site will be 5-10 cm below the elbow joint. The skin should be free from blemishes, scars, heavy hair, veins, moles, skin conditions, sores or tattoos etc. that have the potential to interfere with the detection of local injection site reactions.

Subjects in Group 2 will receive 2 injections to the same forearm, the second injection will be administered approximately 5 cm away radially, not transversely, from the first injection.

Where there is an ongoing injection site reaction an alternative site should be utilised at subsequent vaccination time points. The subsequent vaccination should be located at least 5 cm away from the previous injection site.

Intradermal injections will be carried out by an individual experienced with ID injections as per Appendix 1.

The subject will be instructed to extend their forearm(s) for 10-15 minutes after receiving their vaccination or until the bleb subsides. The injection site will be left open. No cotton wool, adhesive bandages etc. are to be applied over the injection site. The subject will be instructed to avoid touching the injected area(s).

The Investigator or nominee will make the following observations and document findings in the source notes:

- The size of the 'bleb' immediately after injecting in millimetres,
- The size of the 'bleb' during the period that the subject must keep the forearm extended,
- Whether there is an absence of a 'bleb,'
- If the injected material leaked from the skin before 15 minutes,
- If there are any unusual appearances at the injection site.

The subject will be observed for one hour following each vaccination.

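### Time to first recurrence is counted only from dose 1, so it strongly dilutes any effect that needs the full three-dose course; add a Week 9 origin (minor, cheap improvement)

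*Protocol*

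**What the plan says.** The Protocol synopsis and section 4.2 (Exploratory endpoints, Efficacy) fix the origin of the time-to-event endpoint: "Time to first recurrence of symptomatic genital herpes measured from first administration of study vaccine". A companion endpoint is "Number of symptomatic recurrences of genital herpes during the course of the study (to Week 48"), and a symptomatic recurrence rate is listed without a stated window.

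The other efficacy endpoints in the list follow the vaccination course. Shedding is "Number of days with detectable viral shedding after 3-dose vaccination, compared with Baseline", and again after the booster; viral load is handled the same way. Section 6.8.3 gives the schedule: "Vaccinations will occur at: Baseline, Week 4, 8 and a booster will be administered at Week 24". Section 6.4.9 opens the first post-treatment swabbing window one week after dose 3: "Post Vaccination Shedding Assessment - commencing one week following the third investigational vaccine/placebo (Study Period 1"), which is Week 9 (Visit 11).

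Inclusion criterion 2 (section 5.2) requires "at least 3 and no more than 9 reported lesion occurrences in the 12 months prior to Screening", or in the 12 months before suppressive therapy for those taking it. Section 3.3 says that subjects will be monitored for immunological and clinical signs of efficacy before and after the booster.

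**The concern.** A time-to-first-event endpoint uses one event per subject. In people selected because they recur several times a year and who come off suppressive antivirals before the run-in, many of those events will occur before the third dose or shortly after it. Such subjects then add nothing to this endpoint for the rest of follow-up, including the whole booster period.

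If benefit depends on completing the course, the two arms share much of the same early experience. A real later reduction could then show as two similar curves. The shedding and viral-load endpoints avoid this because they wait for the course to finish. The recurrence endpoints do not, although section 3.3 promises a clinical comparison before and after the booster.

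**Working it through.** The protocol gives no power, event count or effect size for this endpoint, so there is no stated figure to reproduce.

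**Inputs from the Protocol.** Recurrence rate r = 3 to 9 per year (5.2); dose 3 at Week 8 and booster at Week 24 (6.8.3); post-course window from Week 9 (6.4.9); follow-up to Week 48 (4.2); 3:1 allocation (4.3) of 40 subjects, giving 30 COR-1 and 10 placebo when the regimens are pooled.

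**Assumptions.** Untreated rate constant and equal to the self-reported history; no dropout; hazard ratios chosen for illustration.

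**1. Share with a first recurrence by week w:** 1 − exp(−r·w/52).

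| r per year | Week 8 | Week 9 | Week 24 |
|---|---|---|---|
| 3 | 37% | 40% | 75% |
| 6 | 60% | 65% | 94% |
| 9 | 75% | 79% | 98% |

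Example: r = 3, w = 9 gives 1 − exp(−0.519) = 0.405.

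**2. Variation between subjects.** With gamma-distributed rates of mean r and shape k, the Week 9 share is 1 − (1 + 9r/(52k))^(−k). For k from 1 to 4 this gives 34–39% at r = 3, 51–60% at r = 6 and 61–73% at r = 9. If the true rate were half the lowest eligible one (1.5 per year), the constant-rate share would still be 1 − exp(−0.260) = 23%.

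**3. Control median:** 52·ln 2/r = 12.0, 6.0 and 4.0 weeks at r = 3, 6 and 9. At 6 and 9 per year it falls before Week 9, so an effect that starts at Week 9 cannot move it. At 3 per year it can: with a hazard ratio of 0.5 from Week 9, the vaccine median is 9 + (12.0 − 9)/0.5 = 15.0 weeks.

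**4. Signal lost.** Simulated log-rank test, two-sided 5%, wins for COR-1 counted, 30 v 10, hazard ratio 0.5, subject rates spread evenly over 3 to 9 per year, at least 4,000 trials per cell. The Week 9 clock takes the first recurrence after Week 9 in every subject.

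| Effect starts | Clock from Day 0 | Clock from Week 9 |
|---|---|---|
| Week 9 | about 7% | about 44% |
| Week 4 | about 16% | about 44% |
| Day 0 | about 44% | about 44% |

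The right-hand column is the same by construction, because the full effect is present from Week 9 in every row; separate runs gave 41% to 45%. By single rate, for a Week 9 onset, the Day 0 clock gives about 14%, 7% and 5% at 3, 6 and 9 per year, against 44–48% from Week 9. At 3 per year with a hazard ratio of 0.3 the Day 0 clock reaches about 27%, against 83%. With a gradual build-up (hazard ratio 0.8 from Week 1, 0.65 from Week 5, 0.5 from Week 9) the Day 0 clock gives 26%, 18% and 13% at 3, 6 and 9 per year. For one regimen alone (15 v 5) and a Week 9 onset, the mixed-rate figures are about 6% and 27%.

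**5. Count to Week 48.** A true rate ratio of 0.50 from Week 9 appears over Day 0 to Week 48 as (9 + 39 × 0.5)/48 = 28.5/48 = 0.59.

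**The case against.** The strongest reply has four parts.

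- **Onset.** The protocol does not say that doses 1 and 2 are inactive. Section 6.3.2.2 samples T-cell responses at Weeks 1 and 5. Week 9 is when swabbing starts, not a documented start of protection. This stands, and is why the size is given for several onsets.
- **Pilot status.** Sections 11 and 11.1 disclaim power and treat any test as descriptive. With 30 v 10, even the Week 9 clock reaches only about 44% at a hazard ratio of 0.5, and pooling regimens is optional. This limits the importance of the point. It does not explain the fall from 44% to 7%, which comes from the clock, and the control median is affected in the same way.
- **Other endpoints.** Subjects who recur early still contribute to the recurrence rate, the Week 48 count, shedding and viral load. This also stands.
- **Time origin.** Timing from first dose is conventional and keeps the randomised comparison whole. That is a good reason to keep it and add to it.

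A reader might infer that the endpoint has almost no ability to show an effect and that both arms must share a median. The low end of the eligible range contradicts this: at 3 per year about 60% are still event-free at Week 9 and the median does move. A reader might also infer that the Week 48 count is equally damaged or takes in the run-in. Its dilution is mild, and section 4.6 sets the 48-week on-study period apart from the run-in.

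**Conclusion.** The point holds as a cheap improvement of minor weight. Section 4.2 itself fixes the origin at dose 1, out of step with the post-course reading of shedding and viral load beside it. At the eligible rates, roughly 40% to 79% of untreated first recurrences fall before Week 9 (34% to 73% with between-subject variation) and 75% to 98% before the booster. The endpoint therefore strongly dilutes an effect that depends on the full course and says little about the booster. How much is lost depends on an onset the protocol does not state: large for Week 9, substantial for Week 4, none for Day 0. The loss is smaller for subjects at 3 recurrences a year.

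The Week 48 count is only mildly diluted; its weakness is that it does not separate the periods before and after the booster. The primary safety conclusions are untouched. The figures rest on constant rates equal to self-reported history, no dropout and illustrative hazard ratios.

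**What to change.** Keep time from first dose. In section 4.2 and the synopsis, add time from Visit 11 (Week 9) to the first new recurrence starting on or after that date, in all subjects still in follow-up, whether or not they recurred earlier. An outbreak already in progress at Visit 11 does not count as new.

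Beside the single count to Week 48, report recurrence rates per person-time for Day 0 to Week 9, Week 9 to 24 and Week 25 to 48, with the run-in rate as baseline. The week between the booster and Visit 17 can be listed separately.

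The cost is endpoint wording in an amendment and matching analysis text. Outbreaks are already asked about at every contact from Visit 2 (Table 1) and recorded on outbreak forms (section 8.11), so no new visits, data or subjects are needed. The downside is that subjects who leave before Week 9 do not contribute to the added analysis, and an effect confined to the first nine weeks would show only in the retained time-from-first-dose endpoint and the Day 0 to Week 9 rate.
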